## Abstract

**Background:**

Large heterogeneity exists in the clinical manifestation of hip osteoarthritis (OA). It is therefore not surprising that pain and disability in individuals with hip OA and after total hip arthroplasty (THA) cannot be explained by biomedical variables alone. Indeed, also maladaptive pain-related cognitions and emotions can contribute to pain and disability, and can lead to poor treatment outcomes. Traumatic experiences, mental disorders, self-efficacy and social support can influence stress appraisal and strategies to cope with pain, but their influence on pain and disability has not yet been established in individuals with hip OA undergoing THA. This study aims (1) to determine the influence of traumatic experiences and mental disorders on pain processing before and shortly after THA (2) to identify preoperative clinical phenotypes in individuals with hip OA eligible for THA, (3) to identify pre- and early postoperative prognostic factors for outcomes in pain and disability after THA, and (4) to identify postoperative clinical phenotypes in individuals after THA.

**Methods:**

This prospective longitudinal cohort study will investigate 200 individuals undergoing THA for hip OA. Phenotyping variables and candidate prognostic factors include pain-related fear-avoidance behaviour, perceived injustice, mental disorders, traumatic experiences, self-efficacy, and social support. Peripheral and central pain mechanisms will be assessed with thermal quantitative sensory testing. The primary outcome measure is the hip disability and osteoarthritis outcome score. Other outcome measures include performance-based measures, hip muscle strength, the patient-specific functional scale, pain intensity, global perceived effect, and outcome satisfaction. All these measurements will be performed before surgery, as well as 6 weeks, 3 months, and 12 months after surgery. Pain-related cognitions and emotions will additionally be assessed in the early postoperative phase, on the first, third, fifth, and seventh day after THA. Main statistical methods that will be used to answer the respective research questions include: LASSO regression, decision tree learning, gradient boosting algorithms, and recurrent neural networks.

**Discussion:**

The identification of clinical phenotypes and prognostic factors for outcomes in pain and disability will be a first step towards pre- and postoperative precision medicine for individuals with hip OA undergoing THA.

**Trial registration:**

ClinicalTrials.gov: NCT05265858. Registered on 04/03/2022.

## Background

Hip osteoarthritis (OA) is one of the leading causes of pain and disability [1–4]. Each year, more than 40 million prevalent cases and more than 2 million incident cases are reported worldwide [3]. The global prevalence and incidence are expected to increase considerably in the upcoming decades, as a result of the aging population and an increasing prevalence of risk factors such as obesity and sedentary lifestyle [1, 5]. Large heterogeneity exists in the clinical manifestation of hip OA, which can be explained by its multifactorial nature and the comorbidities involved [1]. It is therefore not surprising that current conservative treatments according to a one-size-fits-all approach have small to moderate effectiveness [6–8]. Corresponding to the increasing prevalence and incidence of hip OA, the number of total hip arthroplasties (THA) is growing considerably [9]. The mean occurrence rate of hip implants in countries belonging to the Organisation for Economic Co-operation and Development is expected to increase from 145 in 2010 to 275 per 100.000 inhabitants in 2050 [9]. Although THA is considered highly successful in terms of prosthesis-related outcomes, previous studies reported that up to 23% of individuals report long-term pain following THA [10], and over 30% of individuals report limitations in activities of daily living two years after THA [11].

The identification of clinical phenotypes and prognostic factors in individuals with hip OA undergoing THA may help to unravel the complex and heterogeneous nature of hip OA and the prognosis after THA. Clinical phenotypes can be described as subgroups within a given population that are characterized and identified based on a collection of shared clinical characteristics [12, 13]. Several phenotype classifications based on clinical characteristics such as pain sensitization, psychological comorbidities, and radiographic severity have already been found in individuals with knee OA [12, 14]. However, the evidence for clinical phenotypes in individuals with hip OA is limited and has mainly focussed on variables within one domain of the biopsychosocial model [15, 16]. Furthermore, no studies have investigated the existence of clinical phenotypes in individuals after THA for hip OA. The identification of clinical phenotypes in individuals with hip OA undergoing THA can be a first step towards pre- and postoperative precision medicine, as it will allow the development of targeted treatments for specific subgroups [14, 17]. Additionally, prognostic factors for outcomes in pain and disability can inform treatment decisions in individuals eligible for THA, which can be an important step towards the improvement of outcomes after THA [18]. In the current body of research, studies have mainly focused on preoperative candidate prognostic factors and have not considered the role of early postoperative factors in the prognosis of outcome after THA. Biomedical variables, such as comorbidities and radiographic severity, have already been identified as prognostic factors for pain and disability after THA [19, 20]. However, pain and disability in individuals with hip OA and after THA cannot be explained by biomedical variables alone [21].

Indeed, maladaptive pain-related cognitions, emotions, and behavioural factors are known contributors to pain and disability in individuals with musculoskeletal pain, and can lead to poor treatment outcomes [22–30]. Preoperative fear-avoidance behaviour is an important prognostic factor for outcomes after knee and hip surgery [31, 32]. Furthermore, increasing evidence suggests that cognitive appraisals such as perceived injustice contribute to pain and disability in individuals with musculoskeletal disorders, including non-traumatic conditions such as OA [33–36]. Additionally, other psychological and social factors can influence the threat appraisal of pain and the ability to cope with stressful life situations. Evidence suggests that self-efficacy and social support may be associated with the development of disability and the ability to cope with pain [37–39]. Childhood trauma is known to be associated with a higher risk of chronic pain in adulthood, including OA-related pain [40, 41]. Furthermore, traumatic experiences can lead to a significant increase in the risk for mood and anxiety disorders [42, 43]. Symptoms of anxiety are highly prevalent among individuals with hip OA [44] and are known to be associated with higher levels of pain and disability in persons with hip OA and after THA [45]. However, the role of traumatic experiences and mental disorders in the pain processing of individuals with hip OA undergoing THA remains unknown. Furthermore, despite their importance in musculoskeletal disorders, no studies have investigated the existence of clinical phenotypes based on the aforementioned biopsychosocial characteristics, and the prognostic role of factors such as perceived injustice and traumatic experiences has not yet been investigated in individuals undergoing THA for hip OA.

Finally, the heterogeneity in the clinical presentation of individuals with hip OA and in the outcomes after THA may be explained by the pain mechanisms involved [46]. Increasing evidence suggests that central mechanisms play an important role in the pain experience of individuals with hip OA [47]. Widespread hyperalgesia, increased temporal summation of pain, and altered pain modulation through descending inhibitory pain pathways are known indicators of this central involvement [46]. Mechanistic pain profiling using quantitative sensory testing (QST) has already been used to profile individuals with OA based on involved pain mechanisms [48] and is argued to be a promising method to predict the outcomes of pain and disability after total joint arthroplasty [49, 50]. However, the current body of research has not considered both self-reported biopsychosocial variables and mechanistic pain profiling to identify clinical phenotypes in individuals with hip OA undergoing THA.

Therefore, in line with the above identified knowledge gaps, the following objectives were defined: (1) to determine the influence of traumatic experiences and mental disorders on the pain processing of individuals with hip OA and shortly after THA, (2) to identify pre-operative clinical phenotypes in individuals with hip OA and compare their prognosis for outcomes in pain and disability after THA, (3) to identify pre- and early postoperative prognostic factors for long-term outcomes in pain and disability after THA for hip OA, and (4) to identify postoperative clinical phenotypes based on biopsychosocial characteristics at different timepoints up to one year after THA for hip OA, and their pre- and early postoperative prognostic factors.

## Methods

### Study design

A longitudinal prospective cohort study will be conducted to identify clinical phenotypes and prognostic factors for outcomes in pain and disability in individuals with hip OA undergoing THA (HIPPROCLIPS, ClinicalTrials.gov Identifier: NCT05265858). Ethical approval was obtained from the medical ethical committee of Hospital East-Limburg and Hasselt University (B3712021000002). Measurements will be performed at five major timepoints: one week before THA (T0), during the first week after THA (T1), and six weeks (T2), three months (T3), 12 months after THA (T4). During the first week after THA, participants will be asked to complete a minor set of questionnaires on the first, the third, the fifth, and the seventh postoperative day. A timeline and schematic overview of the HIPPROCLIPS-trial can be found in Fig. 1. The HIPPROCLIPS-trial is divided in four sub-studies based on cross-sectional and longitudinal analyses, details on the different studies can be found in Table 1.

**Table 1 Tab1:** Overview of the HIPPROCLIPS-trial studies

Study	Objective	Research Questions (RQ)	Phenotyping variables or candidate prognostic factors	Outcome variables	Design and main statistical method
1	To determine the influence of traumatic experiences and mental disorders on the pain processing of individuals with hip OA and shortly after THA	1. To which extent are traumatic experiences and mental disorders associated with preoperative pain processing in individuals with hip OA waiting for THA? 2. To which extent are traumatic experiences and mental disorders associated with pre- and early postoperative pain-related cognitions and emotions in individuals with hip OA undergoing THA?	- Traumatic experiences (T0) - Mental disorders (T0)	Primary: QST (T0) Secondary: Pain-related cognitions and emotions, other pain-related variables (T0, T1)	**Design**: cross-sectional (RQ1) and longitudinal analysis (RQ2) **Main statistical method**: LASSO regression
2	To identify preoperative clinical phenotypes in individuals with hip OA and their prognosis for outcomes in pain and disability after THA	1. Which clinical phenotypes exist in individuals with hip OA waiting for THA, based on a set of biopsychosocial characteristics? 2. What is the prognostic value of these clinical phenotypes for outcomes in pain and disability after THA?	- Sociodemographic and biomedical information (T0) - Pain-related cognitions and emotions (T0) - Traumatic experiences (T0) - Mental disorders (T0) - Self-efficacy (T0) - Social support (T0) - Perceived stress (T0) - QST (T0) - Other pain-related variables (T0)	Primary: HOOS Secondary: NPRS, PBM, SF-36, PSFS, GPE, Satisfaction, Muscle Strength	**Design**: Cross-sectional analysis of baseline data **Main statistical method**: Decision Tree learning
3	To identify pre- and early postoperative prognostic factors for long-term outcomes in pain and disability after THA in individuals with hip OA	1. To which extent do pre-operative traumatic experiences, mental disorders, pain-related cognitions and emotions, self-efficacy, social support, and central pain mechanisms predict long-term postoperative pain and disability after THA for hip OA? 2. To which extent do early postoperative pain-related cognitions and emotions predict long-term pain and disability after THA for hip OA?	- Pain-related cognitions and emotions (T0) - Traumatic experiences (T0) - Mental disorders (T0) - Self-efficacy (T0) - Social support (T0) - QST (T0)	Primary: HOOS Secondary: NPRS, PBM, SF-36, PSFS, GPE, Satisfaction, Muscle Strength	**Design**: longitudinal prospective **Main statistical method**: Gradient Boosting Algorithms
4	To identify postoperative clinical phenotypes based on biopsychosocial characteristics at different timepoints up to one year after THA for hip OA	1. Which postoperative clinical phenotypes exist based on biopsychosocial characteristics at different timepoints up to one year after THA for hip OA? 2. What is the relationship between preoperative and postoperative clinical phenotypes in individuals with hip OA and after THA? 3. To which extent do pre- and early postoperative factors predict the belonging to a clinical phenotype after THA?	- Sociodemographic and biomedical information (T2, T3, T4) - Pain-related cognitions and emotions (T2, T3, T4) - Traumatic experiences (T2, T3, T4) - Mental disorders (T2, T3, T4) - Self-efficacy (T2, T3, T4) - Social support (T2, T3, T4) - Perceived stress (T2, T3, T4) - QST (T2, T3, T4) - Other pain-related variables (T2, T3, T4)	Primary: HOOS Secondary: NPRS, PBM, SF-36, PSFS, GPE, Satisfaction, Muscle Strength	**Design**: longitudinal prospective **Main statistical method**: Recurrent Neural Networks

*Legend: OA = osteoarthritis, THA = total hip arthroplasty, QST = Quantitative Sensory Testing, NPRS = Numeric Pain Rating Scale, HOOS = Hip Disability and Osteoarthritis Outcome Score, PBM = Performance-Based Measures, SF-36 = 36-item Short-Form Health Survey, PSFS = Patient Specific Functioning Scale, GPE = Global Perceived Effect. Timepoints: one week before THA (T0), during the first week after THA (T1), and six weeks (T2), three months (T3), 12 months after THA (T4)*

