If this approach is not successful, random decision forest will be used [94]. However, it is preferred to keep the model as simple as possible to ease the clinical interpretation.

For the study 3 gradient boosting algorithms will be applied to the dataset to select the best prognostic factors for long-term outcomes in terms of pain and disability [95]. Gradient boosting techniques are a type of ensemble learning that combines numerous weak predictors to create a more accurate one. It adds decision trees to the model in an iterative manner, with each new tree aiming to correct the errors of the preceding trees. Gradient boosting algorithms are especially effective when working with complex data and are frequently capable of achieving high accuracy on a wide variety of problems compared to stepwise linear regression. Previous contralateral THA will be included as a covariate in the analysis to account for possible bias due to knowledge of surgical procedures and postoperative recovery course.

Finally, for study 4, recurrent neural networks (RNN) will be applied to identify postoperative clinical phenotypes based on the multiple data points (repeated measurements during T2, T3, and T4) [96]. RNNs are a sort of neural network architecture that can process sequences of inputs, such as time series. They can keep an internal memory of previous inputs and use it to make predictions about future inputs. RNNs are particularly good for modelling complex temporal interactions. When working with sequential data, RNNs tend to be more flexible and robust than stepwise regression. They are able of modelling complex temporal relationships and less susceptible to overfitting.

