
In addition to the strengths and innovative aspects of this study, there are also some practical issues and potential limitations to consider. In a recent systematic review [101], we investigated contextual prognostic factors for outcomes in the International Classification of Functioning, Disability and Health activity and participation domain after THA in individuals with hip OA. In this review, the main issues in prognostic factor research in individuals after THA for hip OA were discussed. Currently, most studies on prognostic factors for outcomes after THA have a high risk of bias, with mainly problems regarding study attrition and confounding. Therefore, an important practical consideration for this study will be to limit drop-out and accommodate study attrition of participants. The timepoints for follow-up measurements will therefore be scheduled together with the postoperative monitoring appointments with the surgeon to reduce the burden on participants. Furthermore, confounders will be clearly defined and measured using valid and reliable tools, and will be appropriately accounted for in the statistical analysis. One of the limitations of this study will be that generalizability will be limited to individuals with hip OA eligible for THA, and individuals undergoing direct anterior approach THA, since there is a significant preselection of individuals with hip OA undergoing direct anterior approach THA. Furthermore, no external validation is included in this study protocol. When a certain subgroup classification or prognostic factors will be identified, replication of the findings will be necessary in another sample.

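### As specified, the Study 3 prognostic model holds psychosocial and QST factors plus previous contralateral THA only, so it does not show prediction beyond known patient and disease variables

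*Protocol article*

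**What the plan says.** Table 1 of the protocol article gives each sub-study its own list of phenotyping variables or candidate prognostic factors.

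- **Study 2** opens with "Sociodemographic and biomedical information (T0) - Pain-related cognitions and emotions (T0") and goes on to perceived stress and other pain-related variables. Study 4 lists the same domains at the postoperative visits.
- **Study 3** lists six domains, all at T0: pain-related cognitions and emotions, traumatic experiences, then "Mental disorders (T0) - Self-efficacy (T0) - Social support (T0) - QST (T0"). Its first research question names the same six domains, with QST worded as central pain mechanisms.
- **Statistical analysis**, in the paragraph on Study 3: gradient boosting is to pick out the best prognostic factors, and "Previous contralateral THA will be included as a covariate in the analysis". No other covariate is named.
- **Background**: "Biomedical variables, such as comorbidities and radiographic severity, have already been identified as prognostic factors for pain and disability after THA", followed by the argument that "pain and disability in individuals with hip OA and after THA cannot be explained by biomedical variables alone".
- **Discussion**: "confounders will be clearly defined and measured using valid and reliable tools, and will be appropriately accounted for in the statistical analysis". The variables are not named. The Discussion also says that the identified factors may improve the accuracy of prognostic models after THA.

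**The concern.** The Background argues that biomedical variables explain part of the outcome and that something more is needed. That argument leads to a question about what psychosocial and sensory factors add. The Study 3 list leaves out the variables against which an addition would be measured.

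Fear of movement, low self-efficacy or a mental disorder may go together with more comorbidity or more widespread pain. If comorbidity and pain extent are not in the model, a correlated psychosocial score can carry their prognostic information. Gradient boosting does not protect against this, because it gives importance to whichever available variable tracks the outcome. A factor could then rank high in Study 3 while adding nothing to what the clinic already records. This matters most for Study 3, since the sample size was set for its objective.

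**Working it through.** **1. The lists side by side (baseline domains)**

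| Domain | Study 2 | Study 3 |
|---|---|---|
| Sociodemographic and biomedical | yes | no |
| Other pain-related variables | yes | no |
| Perceived stress | yes | no |
| Cognitions/emotions, trauma, mental disorders, self-efficacy, social support, QST | yes | yes |
| Previous contralateral THA | not named | yes (Statistical analysis) |

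The domains missing from Study 3 are collected. Age, sex, height, body weight, number of comorbidities and HOOS are T0 items in Table 2. Pain duration and number of painful regions are described under Other pain-related variables, and Table 1 lists that domain at T0 for Study 2.

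**2. The plan's own sample size**

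Stated inputs: 12 independent variables, 80% power, effect size 0.15, 20% drop-out, total 200. Assumed, because not stated: the effect size is Cohen's f², alpha is 0.05, and the test is the overall F test of a linear regression.

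- Formula: noncentral F with u = 12, v = N − 13 and λ = 0.15 × N.
- Result: 127 completers; 127 / 0.8 = 158.75, so 159 enrolled. The stated 200 is not reproduced under these assumptions. With 90% power the same test needs 157 completers, 197 enrolled, but the text says 80%.
- With 200 enrolled and 20% lost, 160 complete. Power for 12 predictors is then 90.9%.

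**3. Does the planned sample bear a base set?**

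Base set of 8: previous contralateral THA, age, sex, BMI, number of comorbidities, pain duration, number of painful regions, T0 HOOS. The test is the F test for the R² increase of u tested factors over b base variables, with v = N − u − b − 1 and λ = f² × N (partial f² = 0.15, alpha 0.05).

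| Tested factors u | Base b | Completers for 80% power | Enrolled (÷ 0.8) | Power at 160 |
|---|---|---|---|---|
| 12 | 0 | 127 | 159 | 90.9% |
| 12 | 8 | 128 | 160 | 90.7% |
| 22 | 0 | 163 | 204 | 79.0% |
| 22 | 8 | 164 | 205 | 78.7% |

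The 22 is a count from Table 2: three cognition scales, two trauma scales, two MINI-S parts, two HADS subscales, GSES, GO-SSS and 11 QST measures (four thresholds at two sites, VAS 60 temperature, temporal summation, conditioned pain modulation): 3 + 2 + 2 + 2 + 1 + 1 + 11 = 22. The base set costs almost nothing. What moves power is whether 12 or 22 factors are tested.

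**4. Illustration of proxy association (assumed correlations only)**

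Take one psychosocial factor with no added value, correlated 0.3 to 0.5 with one omitted variable that correlates 0.2 to 0.3 with HOOS at 12 months. The induced correlation is the product: 0.3 × 0.2 = 0.06 up to 0.5 × 0.3 = 0.15. With 160 analysed, Fisher's z statistic is atanh(r) × √157: 0.75 for r = 0.06 and 1.89 for r = 0.15. A two-sided 5% test would be passed in about 12% and 47% of studies. This describes a single unadjusted correlation test on assumed inputs. It is not an error rate of the planned gradient boosting.

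**The case against.** A reader might infer that Study 3 leaves out every biomedical variable and therefore cannot show added value. The documents do not support that reading, for four reasons.

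- Previous contralateral THA is biomedical history and is in the analysis, and the Discussion commits to accounting for confounders. An article may leave the exact covariate list to a fuller document.
- Table 1 is not a complete model specification. The second Study 3 question asks "To which extent do early postoperative pain-related cognitions and emotions predict long-term pain and disability after THA for hip OA", yet no T1 variable stands in the Study 3 row. Absence from the row is not proof of absence from the model.
- Added value is not a worded Study 3 question. Both questions ask to what extent the listed factors predict, and a factor can predict without being independent of comorbidity.
- The variables are collected, so nothing prevents adjustment.

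All four stand, and they limit the point to what the article specifies. They do not remove it. The Study 3 row and its first research question agree on the same six domains, the neighbouring rows show that the omitted domains could have been listed, and the one named covariate is justified by knowledge of the procedure and recovery, not by its prognostic weight. A general promise about confounders beside a specific list without the obvious candidates needs to be reconciled.

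**Conclusion.** The point holds in a limited form. On the text of Table 1, the first Study 3 research question and the Statistical analysis section, the Study 3 model has six psychosocial and QST domains plus previous contralateral THA, and none of the sociodemographic, biomedical or other pain-related variables used in Study 2. So specified, it does not show prediction beyond known variables and would not support the Discussion's statement about more accurate prognostic models. To say that it cannot show this would go too far: the data are collected and the promise on confounders leaves room.

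The size of any proxy effect cannot be derived from the documents; the 12% to 47% range is only an illustration. The feasibility result (90.7% power for 12 factors over a base set of 8, 78.7% for 22) rests on an assumed alpha of 0.05, on 0.15 being a partial f², on 160 completers, and on linear regression as a rough guide to gradient boosting. This is an inexpensive improvement, not a flaw that invalidates Study 3.

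**What to change.** Reconcile Table 1 with the Background, the Statistical analysis section and the Discussion:

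1. In the Study 3 row and in the Statistical analysis section, name a base set that always enters the model: previous contralateral THA and T0 age, sex, BMI, number of comorbidities, pain duration, number of painful body regions and HOOS.
2. Beside the planned results, report the cross-validated gain in R² of the psychosocial and QST domains over that base set.
3. State that the 12 independent variables of the sample size calculation exclude the base set, and name the 12.
4. Add the T1 factors needed for the second research question to the Study 3 row.

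Cost: no new data and almost no power. The reported contribution of psychosocial factors may shrink. Radiographic severity, which the Background also calls established, is not among the Table 2 assessments, so the gain would be over the recorded variables only, and the report should say so.

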Quantitative Sensory Testing (QST)	Cold detection threshold (CDT) (local, remote)	T0, T2, T3, T4
	Warmth detection threshold (WDT) (local, remote)	T0, T2, T3, T4
	Cold Pain Threshold (CPT) (local, remote)	T0, T2, T3, T4
	Heat Pain Threshold (HPT) (local, remote)	T0, T2, T3, T4
	VAS 60 Temperature	T0, T2, T3, T4
	Temporal Summation of Pain (TSP)	T0, T2, T3, T4
	Conditioned Pain Modulation (CPM)	T0, T2, T3, T4
**Outcome variables**	**Variables**	**Timepoints**
Self-reported pain and disability	Hip disability and Osteoarthritis Outcome Score (HOOS) [62]	T0, T2, T3, T4
	Patient Specific Functioning Scale (PSFS) [63]	T0, T2, T3, T4
	Numerical Pain Rating Scale (NPRS) [64]	T0, T1, T2, T3, T4
Health-related quality of life	36-item Short-Form Health Survey (SF-36) [65]	T0, T2, T3, T4
Effect of THA on hip complaints in general	Global Perceived Effect (GPE) [66]	T0, T1, T2, T3, T4
Satisfaction with the outcome after THA	Satisfaction (NRS)	T0, T1, T2, T3, T4
Performance-based measures (PBM) [67]	30 s chair stand test (30s-CST)	T0, T2, T3, T4
	40 m fast paced walk test (40 m FPWT)	T0, T2, T3, T4
	10-step stair climb test (10-step SCT)	T0, T2, T3, T4
Muscle strength testing [68]	Isometric muscle strength of the hip flexors, extensors, abductors, adductors, external rotators	T0, T2, T3, T4

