#### Other pain-related variables

Participants will be asked to indicate their pain duration (months), use of pain medication (none, seldom, most days and/or nights, all days and/or nights), number of painful body regions (last week and last year) assessed with a self-created list of body regions, and the number of painful days last week.

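### Study 3 names neither T0 HOOS nor any other preoperative outcome score in its model, so it cannot show whether a factor adds prognostic information beyond preoperative status

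*Protocol article*

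**What the plan says.** All references are to the protocol article.

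- **Candidate factors.** Table 1 (Study design) lists six domains for Study 3, all at T0: pain-related cognitions and emotions, traumatic experiences, mental disorders, and then "Self-efficacy (T0) - Social support (T0) - QST (T0". No T0 pain or function score is listed.
- **Outcomes.** The same row gives "Primary: HOOS Secondary: NPRS, PBM, SF-36, PSFS, GPE, Satisfaction, Muscle Strength".
- **Covariates.** For Study 3 the Statistical analysis section names one: "Previous contralateral THA will be included as a covariate in the analysis to account for possible bias due to knowledge of surgical procedures".
- **Availability.** Table 2 files "Hip disability and Osteoarthritis Outcome Score (HOOS) [62" under outcome variables, at T0, T2, T3 and T4. The abstract confirms the preoperative measurement: "All these measurements will be performed before surgery, as well as 6 weeks, 3 months, and 12 months after surgery".
- **General undertaking.** The Discussion says that "confounders will be clearly defined and measured using valid and reliable tools, and will be appropriately accounted for in the statistical analysis". It does not name a confounder.

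**The concern.** The candidate factors and the T0 outcome scores are collected at the same preoperative visit. The Background itself describes pain-related cognitions, perceived injustice and anxiety as linked to pain and disability. On the authors' own account, then, these factors are likely to track how badly off the patient is before surgery. If preoperative disability also carries over to postoperative HOOS, a factor with no information of its own will still be associated with the outcome.

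The Discussion wants the results to pick out patients likely to do poorly, to inform shared decisions, to seed later trials that target the factors found, and to go hand in hand with careful choice of candidates for THA. Those uses need two kinds of patient to be told apart: one who began worse, and one who ends worse than the starting point would predict. A patient who starts low and gains a great deal could otherwise be flagged by a factor that merely marks the low start. Outcome variance that T0 HOOS could explain also stays in the residual.

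**Working it through.** **1. Is T0 status covered under another name?** In Study 3, no. Table 1 gives Study 2 a longer list, ending "Perceived stress (T0) - QST (T0) - Other pain-related variables (T0". The last of those domains is defined in its own section ("Participants will be asked to indicate their pain duration (months), use of pain medication", then painful body regions and painful days). It contains neither HOOS nor NPRS, and it is not in the Study 3 list. The sample size paragraph mentions 12 independent variables but does not itemise them.

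**2. The plan's own figure.** The sample size of 200 is based on this objective: 12 predictors, 80% power, effect size 0.15, 20% dropout. Reading 0.15 as f², assuming alpha 0.05 and using the overall F test (noncentrality λ = f²N, degrees of freedom u and N − u − 1), 127 completers are needed. Then 127 / 0.8 = 158.75, so 159, not 200. That mismatch is a separate matter. The calculation is used here only to cost the fix in step 5.

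**3. Induced association.** Let X be a factor with no effect beyond T0 HOOS. Then

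r(X, postoperative HOOS) = r(X, T0 HOOS) × r(T0 HOOS, postoperative HOOS).

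The article gives neither correlation. Assuming 0.2 to 0.5 for each, the product runs from 0.2 × 0.2 = 0.04 to 0.5 × 0.5 = 0.25.

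**4. How often X looks prognostic.** Completers: 200 × (1 − 0.20) = 160. The figures come from 4,000 simulated datasets per setting, with a two-sided 5% linear test standing in for boosting. Share of datasets in which X is significant when T0 HOOS is left out:

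| r(X, T0 HOOS) | r(T0, post) 0.2 | 0.3 | 0.4 | 0.5 |
|---|---|---|---|---|
| 0.2 | 8% | 12% | 17% | 24% |
| 0.3 | 12% | 21% | 33% | 47% |
| 0.4 | 17% | 32% | 53% | 71% |
| 0.5 | 24% | 47% | 72% | 89% |

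With T0 HOOS in the model the share is 4% to 6% in every cell.

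Check by Fisher z, with standard error 1/√157: for r = 0.25, atanh(0.25) × √157 = 0.2554 × 12.53 = 3.20, and Φ(3.20 − 1.96) = 0.89, which agrees with the bottom right cell.

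Over the same range T0 HOOS would explain 0.2² = 4% to 0.5² = 25% of the outcome variance.

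**5. Price of adding it.** At 160 completers λ = 0.15 × 160 = 24. Power is 90.9% with 12 predictors (df 12, 147) and 89.7% with 13 (df 13, 146), a loss of 1.2 points. The required number rises from 127 to 131 completers, and 131 / 0.8 = 163.75, so 164, which is still below 200.

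**The case against.** **The list may not be the whole model.** The Table 1 column is for phenotyping variables and candidate prognostic factors, not for adjustment variables. It omits contralateral THA, which the text does include, and it omits the early postoperative factors that Study 3's second research question concerns. The text does not call contralateral THA the only covariate, the Discussion promises to deal with confounders, and a condensed article may leave the full set to an analysis plan. This stands against reading the plan as *excluding* baseline adjustment, which the documents do not say. It does not remove the point. The article prints a predictor list and names and justifies one covariate, and the most obvious candidate, already collected, is in neither. A general promise that names nothing does not fill that gap.

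**The percentages are not error rates for the stated question.** A factor with r = 0.04 to 0.25 with the outcome does predict it, and the research question asks about prediction. This is right. The 8% to 89% is the chance of detecting a real marginal association. It becomes a wrong answer only when read as value beyond preoperative status. The correlations are assumed, and the plan uses boosting, not this test.

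**T0 HOOS may be a mediator.** Trauma, self-efficacy or social support may act partly through preoperative disability. Conditioning on T0 HOOS then hides part of their prognostic role. This stands too, and it is why an adjusted model alone would go too far.

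**Conclusion.** The point holds for Study 3, as a gap in the model as stated. A factor that only tracks preoperative pain and disability *can* be selected as prognostic, and the stated analysis cannot show whether it adds to preoperative status. A reader might infer that this *will* happen. The documents give no correlations that would support that, and the 8% to 89% range illustrates how far the answer depends on them. It rests on 160 completers, correlations of 0.2 to 0.5, no effect beyond T0 HOOS, and a linear test.

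A reader might also extend the charge to Study 2, whose second question compares the prognosis of the phenotypes on the same outcomes. The documents do not support calling that an error. The Statistical analysis section describes only the tree that forms the phenotypes and gives no prognosis model from which anything could be missing. That HOOS is absent from the phenotyping variables is no evidence either way.

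**What to change.** In Study 3:

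1. Add the T0 value of the outcome being analysed as a forced base term: T0 HOOS for HOOS, and likewise for NPRS, the performance-based measures, SF-36, PSFS and muscle strength. Global perceived effect and satisfaction are also scheduled at T0 in Table 2, but they rate the result of surgery and have no meaningful preoperative counterpart.
2. Fit it first rather than merely offering it to the algorithm, because a boosted tree need not split on a variable it is offered.
3. Report the cross-validated gain of the candidate factors beyond that base.
4. Show the model without the T0 outcome alongside, and say that the two answer different questions: overall prediction, and prediction beyond preoperative status.

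This means adding the T0 outcome to the Study 3 row of Table 1 and a sentence or two to the Statistical analysis section. The cost is one extra predictor, about one point of power on the assumptions above, and a second model to report. No data beyond those already scheduled are needed. The same adjustment can be applied when the Study 2 phenotypes are compared on outcome.
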